## Abstract

**Background:**

Radiation therapy is an essential modality in the treatment of breast cancer. Addition of radiotherapy to surgery has significantly increased local control and survival rates of the disease. However, radiotherapy is also associated with side effects, such as tissue fibrosis or enhanced vascular morbidity. Modern radiotherapy strategies, such as intensity modulated radiotherapy (IMRT), can shorten the overall treatment time by integration of the additional tumor bed boost significantly. To what extent this might be possible without impairing treatment outcome and cosmetic results remains to be clarified.

**Methods/Design:**

The IMRT-MC2 study is a prospective, two armed, multicenter, randomized phase-III-trial comparing intensity modulated radiotherapy with integrated boost to conventional radiotherapy with consecutive boost in patients with breast cancer after breast conserving surgery. 502 patients will be recruited and randomized into two arms: patients in arm A will receive IMRT in 28 fractions delivering 50.4 Gy to the breast and 64.4 Gy to the tumor bed by integrated boost, while patients in arm B will receive conventional radiotherapy of the breast in 28 fractions to a dose of 50.4 Gy and consecutive boost in 8 fractions to a total dose of 66.4 Gy.

**Discussion:**

Primary objectives of the study are the evaluation of the cosmetic results 6 weeks and 2 years post treatment and the 2- and 5-year local recurrence rates for the two different radiotherapy strategies. Secondary objectives are long term overall survival, disease free survival and quality of life.

**Trial Registration:**

ClinicalTrials.gov Protocol ID: NCT01322854.

## Background

Breast cancer is the most common cancer entity in women in developed countries, representing a major health care problem. The disease is diagnosed in about 1.2 million patients and accounts for about 500,000 deaths yearly worldwide [1]. Treatment is based on stage, histology and biomarkers and is commonly multimodal. The development of diagnostic strategies has led through the years to an earlier diagnosis of breast cancer, which resulted in the evolution from entirely surgical treatment into more conservative approaches, replacing mastectomy by breast-conserving surgery followed by radiation therapy in early-stage disease [2]. Adjuvant whole-breast external beam radiotherapy has been shown to result in a significant increase of local control, as well as a significant reduction in the risk of death [3], making the outcome of breast-conserving surgery comparable to mastectomy. Furthermore, additional boost-irradiation to the tumor bed is found to further improve local tumor control. In particular, 10-year cumulative incidence of local relapse in the randomized prospective trial comparing whole-breast irradiation versus whole-breast irradiation and subsequent boost was 10.2% versus 6.2% [4]. Further analyses have revealed an increased benefit for patients younger than 50 years and patients with high grade invasive ductal carcinoma [5].

The most common adjuvant radiotherapy strategy after breast-conserving surgery consists of irradiation of the whole breast using two tangential photon beams during a 5-6 week period, with doses of 1.8-2.0 Gy per fraction to a total dose of approximately 50 Gy. Thereafter, boost irradiation is carried out using electrons and/or photons up to a total dose of 66 Gy, resulting in total treatment duration of 7-8 weeks.

Dose escalation by a sequential boost regimen results in a longer treatment duration. Furthermore, various studies have demonstrated that higher radiation dose is associated with a limited but statistically significant worsening of the cosmetic result, mainly due to breast fibrosis. In particular, the risk of moderate or severe fibrosis at 10 years after breast conserving surgery followed by whole breast irradiation with or without boost-irradiation of 16 Gy was significantly increased for the group of patients that had received a boost (12.6% versus 26.9%) [6].

Another important aspect in radiation therapy of breast cancer is the fact that although radiotherapy is associated with reduced disease-specific mortality, an increase of cardiovascular mortality after radiation treatment has been shown, with a trend towards higher risk for women with left-sided disease [7]. Radiation associated cardiac disease can manifest either as acute injury, i.e. pericarditis, or as late injury, such as congestive heart failure, ischemia, coronary artery disease or myocardial infarction months to years post radiation therapy [8]. Volume-dependent perfusion defects after irradiation of left-sided breast cancer using tangential photon beams to a dose of 50 Gy and electron boost of 16-18 Gy has been revealed for up to 40% of patients within 2 years after treatment [9]. The risk for heart disease post-irradiation is higher for younger patients and is further enhanced by the established use of anthracyclines in multimodal treatment regimes [10].

The limitations in radiation therapy of breast cancer reveal the necessity for the use of advanced radiation therapy strategies that allow a more accurate delivery of radiation dose to the target volume sparing the surrounding healthy tissues. A promising technology to achieve this goal is intensity modulated radiotherapy (IMRT). IMRT is an advanced technique using computer-assisted inverse planning and administering radiation via multiple individual segments. Varying intensities across each beam allow improvement of dose homogeneity. Delivery of irradiation to irregularly shaped targets is optimized with IMRT, while the technology offers the ability to produce concavities in the treatment volume and therefore increase conformality. Trials in breast cancer patients have demonstrated better dose uniformity throughout the breast for intensity modulated radiotherapy with a median of 0.1% of the treatment volume receiving ≥110% of the prescribed dose versus 10% with conventional wedges [11]. Helical tomotherapy is an advanced technology for intensity modulated radiotherapy using an image-guided, dynamic, therapy delivery system, which offers the potential for pretreatment megavoltage CT imaging. Pretreatment imaging for patient positioning verification is of high importance, since it allows corrections for inter-fraction positioning errors, which is a prerequisite for accurate delivery of complex IMRT treatment plans [12]. Studies in breast cancer patients comparing tomotherapy with 3D-planning demonstrated a minimal dose increase but improved dose homogeneity and conformity to the planning target volume [13].

A major advantage of IMRT is also the fact that, in contrast to conventional techniques, it provides the possibility to integrate the boost concept in the daily radiation sessions by increasing the dose per fraction within the boost volume [14]. Hence, overall treatment duration can be shortened by more than one week compared to conventional radiation treatment in patients, who are likely to benefit from an additional boost to the tumor bed.

Thus, aim of this prospective, two-armed, multicenter, randomized trial is to compare the results of intensity-modulated radiotherapy versus conventional radiotherapy for adjuvant treatment of breast cancer. Rationale of the project is the reduction of treatment duration in view of at least consistent radiation toxicity, local control, disease-free survival and overall survival, with emphasis given to the cosmetic results and local control after adjuvant treatment.

## Methods/Design

### Trial organization

The trial has been designed by the study initiators at the Department of Radiation Oncology and the Department of Gynecology of the University of Heidelberg. The trial is carried out at the University of Heidelberg, Department of Radiation Oncology and Department of Radiation Oncology, University Medical Center Mannheim. The University of Heidelberg is responsible for trial management and coordination, as well as quality assurance including reporting, monitoring and database management.

### Study design

IMRT-MC2 is a prospective, two-armed, multicenter, randomized, phase III trial. The trial workflow and treatment arms are depicted in Figure 1.

**Figure 1 F1:**
[figure not shown]
**Trial flow-chart**.

Patients fulfilling the inclusion criteria will be randomized into two arms:

#### Arm A- Experimental Arm

IMRT of the whole residual breast to a total dose of 50.4 Gy and 1.8 Gy per fraction with 2.3 Gy per fraction within integrated boost to the tumor bed to a total dose of 64.4 Gy in 28 fractions.

#### Arm B- Conventional Arm

Conventional radiotherapy of the whole residual breast to a total dose of 50.4 Gy and 1.8 Gy per fraction in 28 fractions, followed by consecutive boost to a total dose of 66.4 Gy and 2 Gy dose per fraction in 8 fractions. A total of 36 fractions is given to patients included in arm B.

### Study objectives

Primary objectives of the study are cosmetic result and local control rate after radiotherapy. The cosmetic result will be evaluated at 6 weeks and 2 years post radiotherapy. Local control will be evaluated at 2 and 5 years post treatment.

Secondary objectives of the trial are quality of life at 6 weeks and 2 years after radiotherapy, as well as overall survival and disease free survival at 6 weeks, 2, 5, 10 and 15 years post radiation treatment.

### Investigators

Patient treatment will be performed by radiation oncologists at the Department of Radiation Oncology at the University of Heidelberg and the Department of Radiation Oncology at the University Medical Center Mannheim.

### Data Handling, Storage and Archiving

All findings including clinical and laboratory data will be documented by the investigator or an authorized member of the study team in the subject's medical record and eCRF (electronic Case Report Form). The investigator is responsible for ensuring that all sections of the eCRF are completed correctly and that entries can be verified against source data. In some cases, the eCRF, or part of the eCRF, may also serve as source documents: Karnofsky Performance Status, Documentation of Cosmetic Result and Clinical Examination.

Data will be collected and entered in a study specific database by the Study Center of the Department of Radiation Oncology at the University of Heidelberg and the Study Center of the Department of Radiation Oncology at the University Medical Center Mannheim.

All missing data or inconsistencies will be reported back to the investigators and clarified by the responsible investigator. If no further corrections are to be made in the database it will be declared closed and used for statistical analysis.

The data will be stored and archived according to §13 of the German GCP-Regulation and §28c of the German X-Ray Regulation (RöV) and §87 of the German Radiation Protection Regulation (StrlSchV) for at least 30 years after the trial termination.

Data management for this study will be coordinated by the Coordination Centre for Clinical Trials (KKS) Heidelberg.

### Ethics, informed consent and safety

The final protocol was approved by the University of Heidelberg ethics committee (S-041/2009) and the Federal Office of Radiation Protection (BfS) (Z5-22461/2-2009-018). The trial is sponsored by the German Aerospace Center (DLR)/Federal Ministry of Education and Research (BMBF) of Germany (01ZP0504). This study complies with the Helsinki Declaration and its recent German version, the Medical Association code of conduct, the principles of Good Clinical Practice (GCP) and the Federal Data Protection Act. The trial will be carried out in keeping with local legal and regulatory requirements. The medical secrecy and the Federal Data Protection Act will be followed. The ClinicalTrials.gov Protocol ID is NCT01322854.

### Patient selection

#### Inclusion criteria

Patients meeting the following criteria will be considered for admission to the trial:

• All patients aged >18 years and <70 years after breast conserving surgery.

• Patients aged ≥70 years with following risk factors:

○ Tumor stage ≥T2

○ Multifocal disease

○ Lymphangiosis

○ Extended intraductal component

○ Resection margin ≤3 mm

### Exclusion criteria

Patients presenting with one of the following criteria will not be included in the trial:

• Refusal of the patients to be included in the study

• Karnofsky Performance Score ≤70%

• Metastatic disease (M1)

• Other malignancies

• Previous radiotherapy of the breast

• Pregnancy

### Study plan

502 patients (251 patients in each arm) with breast cancer and previous breast conserving surgery are included in the study according to the criteria above. Eligible patients are informed about participation in the trial with possible benefits and risks, and written informed consent is obtained. Patients are randomized into the two treatment arms after baseline photo-documentation and evaluation of the postoperative cosmetic result through an expert panel and the patient, as well as evaluation of life quality using an EORTC questionnaire.

### Treatment planning and radiation therapy

#### Arm A

After reliable patient positioning, a thoracic CT scan with a slice distance of 3 mm is carried out. Based on the CT data set, radiation treatment planning is performed as inverse planning using the planning tool KonRad^® ^(Siemens OCS, Erlangen, Germany). Multiple fields arranged in a star-shape around the ipsilateral hemithorax are chosen. Intensity modulation is optimized according to the specified dose directions applying an inverse treatment planning technique. 6 MV-photons are used for irradiation. IMRT can be applied either in step-and-shoot technique at a linear accelerator or at a dedicated tomotherapy unit. During treatment, regular image guidance via MV-CT is carried out for positioning control.

The clinical target volume (CTV) for the residual breast tissue and - in certain cases - the locoregional lymphatics, will be defined according to the S3 guidelines of the German Cancer Society [15]. The CTV for Arm A includes the residual breast up to 5 mm under the skin surface. The primary target volume (PTV) includes the CTV with a margin of 10 mm in all directions when optimization via virtual bolus concept is possible. In Arm A/Tomotherapy or Arm A/IMRT without virtual bolus concept the PTV will not be extended over the skin surface. The GTV includes the tumor bed, as defined by preoperative mammography.

IMRT treatment is performed in 28 fractions with 1.8 Gy per fraction to a total dose of 50.4 Gy and integrated boost with 2.3 Gy per fraction to a total dose of 64.4 Gy. This is equivalent to the dose of the conventional treatment arm in consideration of the linear-quadratic model. CTV will be covered by 45 Gy, GTV will be covered by 95% of the prescribed dose i.e. 60.8 Gy. With regard to the organs at risk, less than 10% of the heart volume may receive >30 Gy, while less than 20% of the ipsilateral lung may receive more than 20 Gy. The mean dose to the contralateral breast should be limited to less than 5 Gy.

In case dose to the target volume and dose limits to the organs at risk can not be met at the same time, compliance with the threshold dose in the target volume is paramount. However, dose limitations in contralateral structures have to be met.

Treatment duration is 5^3/5 ^weeks with 5 fractions per week.

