#### Arm B

Patient positioning can be performed according to the standards of the participating medical centers and will be controlled weekly by conventional verification films. For treatment in Arm B thoracic scans with a slice distance of 10 mm are allowed.

The clinical target volume (CTV) includes the residual breast to the skin surface and in certain cases the locoregional lymphatics, according to the S3 guidelines of the German Cancer Society [15]. The primary target volume (PTV) includes the CTV with a medio-lateral and cranio-caudal margin of 10 mm, as well as a ventral margin of 20 mm. The GTV includes the tumor bed, as defined by preoperative mammography.

Conventional radiation treatment of the residual breast is performed in 28 fractions with 1.8 Gy per fraction to a total dose of 50.4 Gy. Subsequently, a consecutive boost to the tumor bed is carried out with 2 Gy per fraction in 8 fractions to a total dose of 66.4 Gy. Patients treated in Arm B receive a total of 36 fractions.

CTV will be covered by 45 Gy, GTV will be covered by 95% of the prescribed dose, i.e. 63.1 Gy. In regard to the organs at risk, less than 10% of the heart volume may receive >30 Gy, less than 40% of the ipsilateral lung may receive >20 Gy, while the mean dose in the contralateral breast should be less than 5 Gy.

In case dose to the target volume and dose limits to the organs at risk can not be met at the same time, compliance with the threshold dose in the target volume is paramount. However, dose limitations in contralateral structures have to be met.

Treatment duration is 7^1/5 ^weeks with 5 fractions per week.

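### The Arm A tumour-bed coverage dose does not match its own rule: 95% of the prescribed 64.4 Gy is 61.2 Gy, not 60.8 Gy

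*Protocol article*

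**What the plan says.** The protocol article gives the Arm A tumour-bed prescription in three places, always with the same value. The abstract (Methods/Design) describes the arm as "delivering 50.4 Gy to the breast and 64.4 Gy to the tumor bed by integrated boost". The arm description under Study design has "2.3 Gy per fraction within integrated boost to the tumor bed to a total dose of 64.4 Gy in 28 fractions". The Arm A part of Treatment planning and radiation therapy has "integrated boost with 2.3 Gy per fraction to a total dose of 64.4 Gy".

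That last section then sets the coverage requirement for the tumour bed: "GTV will be covered by 95% of the prescribed dose i.e. 60.8 Gy". It adds that, where target dose and organ-at-risk limits cannot both be met, "compliance with the threshold dose in the target volume is paramount", with the contralateral limits excepted.

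The Arm B section states the same rule for its own prescription of 66.4 Gy: "GTV will be covered by 95% of the prescribed dose, i.e. 63.1 Gy".

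**The concern.** The Arm A sentence states one threshold twice, as a percentage and as a dose, and the two differ. The Gy value is offered as a restatement of the 95% rule, so it should follow from the prescription given just before it. It does not.

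The sentence belongs to the treatment instructions, and the target threshold takes precedence over the organ-at-risk limits other than the contralateral ones. With two values in the text, a plan covering the tumour bed with 61.0 Gy would pass on the Gy figure and fail on the percentage. Patients are treated at two centres, which could in principle read the sentence differently. If the Gy value were used, only the experimental arm would be planned to a looser relative criterion, in a non-inferiority trial that has local control as one of its two primary endpoints.

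**Working it through.** **Inputs (all from the protocol article)**

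- Arm A: 28 fractions, 2.3 Gy per fraction to the tumour bed, total 64.4 Gy; coverage 95%, printed as 60.8 Gy (Treatment planning, Arm A).
- Arm B: 28 fractions of 1.8 Gy, then 8 of 2 Gy, total 66.4 Gy; coverage 95%, printed as 63.1 Gy (Treatment planning, Arm B).

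**Step 1: the prescriptions.** Both totals are correct.

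- Arm A: 28 × 2.3 = 64.4 Gy
- Arm B: 28 × 1.8 + 8 × 2 = 50.4 + 16 = 66.4 Gy

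**Step 2: apply the rule, coverage dose = 0.95 × prescription.**

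| Arm | Prescription | 95% of it | Printed | Printed ÷ prescription |
|---|---|---|---|---|
| A | 64.4 Gy | 61.18 Gy | 60.8 Gy | 94.4% |
| B | 66.4 Gy | 63.08 Gy | 63.1 Gy | 95.0% |

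Arm B reproduces to the printed decimal; Arm A does not. The Arm A gap is 61.18 − 60.8 = 0.38 Gy, and 0.38 ÷ 64.4 = 0.59% of the prescription.

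**Step 3: can rounding explain it?**

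- *Percentage rounded to 95%.* Values from 94.5% to 95.5% give 0.945 × 64.4 = 60.86 Gy to 0.955 × 64.4 = 61.50 Gy. The printed 60.8 Gy lies outside this range.
- *Result rounded to 60.8 Gy.* The prescription would have to lie between 60.75 ÷ 0.95 = 63.95 Gy and 60.85 ÷ 0.95 = 64.05 Gy, or 2.284 to 2.288 Gy per fraction over 28 fractions. The article states no such dose.
- *Prescription rounded to whole Gy first.* 0.95 × 64 = 60.8 Gy, which matches. But the same practice in Arm B would give 0.95 × 66 = 62.7 Gy, against 63.1 Gy printed.

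**Step 4: other readings.** The boost contributes 64.4 − 50.4 = 14 Gy.

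- 95% of the fraction dose, rounded, times 28: 0.95 × 2.3 = 2.185; 2.18 × 28 = 61.04 Gy, or 2.2 × 28 = 61.6 Gy.
- 95% of the breast dose plus the full boost: 0.95 × 50.4 + 14 = 61.88 Gy.
- Full breast dose plus 95% of the boost: 50.4 + 0.95 × 14 = 63.7 Gy.

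None gives 60.8 Gy.

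**Step 5: what the printed value implies between arms.** Taken literally, the criteria are 94.4% in Arm A and 95.0% in Arm B. The Arm A fraction applied to Arm B would give 0.9441 × 66.4 = 62.7 Gy rather than 63.1 Gy.

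**The case against.** The best opposing argument concerns importance, since the arithmetic is not in dispute. The rule is written out in words beside the prescription and repeated for Arm B, so the natural reading is that 95% governs and the Gy figure is a faulty gloss. A planner who reads it that way uses 61.2 Gy, and the arms have the same relative criterion. The gap is 0.6% of the dose, and 60.8 Gy falls only 0.06 Gy below the lowest value that rounds to 95%. Nothing in the statistical sections uses the figure. Nor does the article show that a 0.38 Gy shift would create or resolve any conflict with an organ-at-risk limit.

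Moreover, this is a journal article condensed from a full protocol that is not shown. Planners may never have worked from it, and the full protocol may carry the right number. The origin of 60.8 Gy is also unknown: a calculation from a prescription rounded to 64 Gy is as possible as a printing slip.

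All of this stands, and it fixes the rating at minor. It does not remove the inconsistency: the article states the value wrongly, and the Arm B sentence shows which value the rule should have produced.

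**Conclusion.** The point holds, as a minor one. The Arm A coverage dose is understated by 0.38 Gy (0.6% of the prescription) relative to the rule printed with it. This rests only on the 64.4 Gy prescription, stated consistently in three places and equal to 28 × 2.3 Gy, and on taking the stated 95% as intended, which Arm B supports.

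What is established is an error in the article's text. It is not established that any patient was planned to 60.8 Gy, that the between-arm comparison was affected, or how the wrong number arose. The sample size, the non-inferiority margins and the analysis methods do not depend on it.

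**What to change.** In the Arm A part of Treatment planning and radiation therapy, change 60.8 Gy to 61.2 Gy, which agrees with the stated rule and with Arm B. If 60.8 Gy was chosen on purpose, keep it and give its true percentage, 94.4%, in place of 95%.

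Then check the full protocol. If it has the same figure, send a short note to the planners at both centres; if not, correcting the article is enough. The cost is one number and, at most, that note.

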#### Arm B

Patient positioning can be performed according to the standards of the participating medical centers and will be controlled weekly by conventional verification films. For treatment in Arm B thoracic scans with a slice distance of 10 mm are allowed.

The clinical target volume (CTV) includes the residual breast to the skin surface and in certain cases the locoregional lymphatics, according to the S3 guidelines of the German Cancer Society [15]. The primary target volume (PTV) includes the CTV with a medio-lateral and cranio-caudal margin of 10 mm, as well as a ventral margin of 20 mm. The GTV includes the tumor bed, as defined by preoperative mammography.

Conventional radiation treatment of the residual breast is performed in 28 fractions with 1.8 Gy per fraction to a total dose of 50.4 Gy. Subsequently, a consecutive boost to the tumor bed is carried out with 2 Gy per fraction in 8 fractions to a total dose of 66.4 Gy. Patients treated in Arm B receive a total of 36 fractions.

CTV will be covered by 45 Gy, GTV will be covered by 95% of the prescribed dose, i.e. 63.1 Gy. In regard to the organs at risk, less than 10% of the heart volume may receive >30 Gy, less than 40% of the ipsilateral lung may receive >20 Gy, while the mean dose in the contralateral breast should be less than 5 Gy.

In case dose to the target volume and dose limits to the organs at risk can not be met at the same time, compliance with the threshold dose in the target volume is paramount. However, dose limitations in contralateral structures have to be met.

Treatment duration is 7^1/5 ^weeks with 5 fractions per week.

